### 1.5.2 SECOND DOSE ESCALATION AND EVALUATION

Following a review of the cumulative safety data and preliminary immune responses in the first dose escalation cohort on 18th August, the Trial Steering Committee recommended that the trial team evaluate higher doses up to 10 µg. As of 9th August, 120 participants age 18-45 were enrolled to the 3 dose groups, 15 of whom had received their second vaccination. Reactions reported in the first 7 days were absent or mild with the most common local mild reaction being tenderness/discomfort (43%) followed by pain (15%). These appear to increase with dose. The most common mild systemic reactions are fatigue (25%) and headache (23%) with no clear relationship to dose. Moderate reactions have been infrequent: tenderness/discomfort and pain reported by 2% and 1% respectively; fatigue by 3% and headache by 3%. Preliminary immune responses suggested a dose response with earlier responses seen at higher doses, but no more than half the participants in the 0.1 and 0.3 µg groups had seroconverted. Insufficient data were available on the 1 µg group but the overall consensus was that the doses explored to date were too low.

The second dose escalation cohort will proceed through 2.5, 5 and 10 µg as follows over the course of 11 days (minimum):

1. The first participant will receive 2.5 µg and be invited to enter information on local and systemic reactions, into an online diary, that evening and daily thereafter for 6 days.
2. At 48 (-/+5) hours post-vaccination the team will call the first participant and go through his/her diary. If the reactions are Grade 1-2, or transient Grade 3 that resolve within 24 hours, three further participants may receive 2.5 µg
3. At 48 (-/+5) hours post-vaccination the team will call the next three participants and go through their diaries. If the reactions are Grade 1-2, or transient Grade 3 that resolve within 24 hours, a sentinel participant may receive 5 µg.
4. At 48 (-/+5) hours post-vaccination the team will call the sentinel participant at 5 µg vaccinated in Step 3 and go through his/her diary. If the reactions are Grade 1-2, or transient Grade 3 that resolve within 24 hours, three further participants may receive 5 µg.
5. At 48 (-/+5) hours post-vaccination the team will call the three participants vaccinated in Step 4 and go through their diaries. If the reactions are Grade 1-2, or transient Grade 3 that resolve within 24 hours, a sentinel participant may receive 10 µg.
6. At 48 (-/+5) hours post-vaccination the team will call the sentinel participant vaccinated in Step 5 and go through his/her diary. If the reactions are Grade 1-2, or transient Grade 3 that resolve within 24 hours, three further participants may receive 10 µg.
7. At 48 (-/+5) hours post-vaccination the team will call the three participants vaccinated in Step 6 and go through their diaries. When all four participants to receive 10 µg have attended their follow-up visits at Day 7, the safety data accrued to date will be reviewed and, if deemed

acceptable using the same criteria described above, the second dose evaluation cohort of 60 participants may start to be enrolled to receive 2.5, 5 or 10 µg

The steps above describe the fastest dose escalation plan from 2.5–10 µg. However, if there are persistent Grade 3 reactions observed in any of the sentinels, the team will invite the affected participant to attend the study site in order to evaluate these and will proceed to vaccinate a second sentinel at the same dose. The dose will not be escalated until at least 1 participant has provided acceptable safety data to at least 48 (–/+5) hours post-vaccination. If 2 or more of the participants at any dose level in the dose escalation part of the trial have persistent Grade 3 (or worse) reactions, or if 1 or more has a serious adverse reaction, the dose will not be escalated or expanded, and the trial stopping rules described below will be triggered.

**Figure 7. Fastest possible first dose escalation plan, provided there are no persistent Grade 3 (severe), or serious, reactions**

[figure not shown]

 This is the fastest possible dose escalation plan; it is not a fixed schedule. Reasons for a slower dose escalation include persistent Grade 3 or serious reactions, availability of participants and staff, and other operational factors.

**Figure 8. Fastest possible second dose escalation plan, provided there are no persistent Grade 3 (severe), or serious, reactions**

[figure not shown][figure not shown]

 This is the fastest possible dose escalation plan; it is not a fixed schedule. Reasons for a slower dose escalation include persistent Grade 3 or serious reactions, availability of participants and staff, and other operational factors.

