| Study Design                                         | 
The study has three components:
 
 
➤ Open-label, non-randomised dose escalation in 15 individuals aged 18-45 years enrolled through a single centre
 
➤ Randomised dose evaluation in 105 individuals aged 18-45 years enrolled through a single centre. Participants and laboratory staff will be blind to allocation.
 
➤ Open-label, expanded safety evaluation of the highest dose (1 µg) in at least a further 200 individuals aged 18-75 years enrolled through multiple centres
 
 
As part of an amendment to protocol v5.0 a new cohort will be recruited to assess higher dose levels as follows:
 
 
➤ Open-label, non-randomised dose escalation in 12 individuals aged 18-45 years.
 
➤ Non-randomised dose evaluation in 60 individuals aged 18-45 years. Participants and laboratory staff will be blind to allocation.
 
 
In addition participants in the open-label, expanded safety evaluation will be able to delay their second injection until the safety data following the first vaccinations with the higher doses are available. They will be offered the option of the highest dose studied for their second injection, provided this is well tolerated.
 |

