The steps above describe the fastest dose escalation plan. However, if there are persistent Grade 3 reactions observed in any of the sentinels, the team will invite the affected participant to attend the study site in order to evaluate these and will proceed to vaccinate a second sentinel at the same dose. The dose will not be escalated until 4 participants in total have provided safety data to at least 48 hours post-vaccination. If 2 or more of the participants at any dose level in the dose escalation part of the trial have persistent Grade 3 (or worse) reactions, or if 1 or more has a serious adverse reaction, the dose will not be escalated or expanded, and the trial stopping rules described below will be triggered.

The dose escalation plan described above will be repeated when the participants return for their second vaccinations at Week 4.

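### After a persistent Grade 3 reaction in a sentinel, Section 1.5.2 asks for one participant with acceptable 48-hour data before escalating, where Section 1.5.1 asks for four in total

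*Protocol*

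**What the plan says.** Protocol Sections 1.5.1 (0.1, 0.3 and 1.0 µg) and 1.5.2 (2.5, 5 and 10 µg) each set out numbered or bulleted steps, described as the fastest plan, followed by a paragraph for the case where a sentinel has a persistent Grade 3 reaction. In both paragraphs the affected participant is evaluated and a second sentinel is vaccinated at the same dose. The sentence on escalation then differs:

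- Section 1.5.1: "The dose will not be escalated until 4 participants in total have provided safety data to at least 48 hours post-vaccination".
- Section 1.5.2: "The dose will not be escalated until at least 1 participant has provided acceptable safety data", to at least 48 (±5) hours.

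The stopping sentence that follows is the same in both: "If 2 or more of the participants at any dose level in the dose escalation part of the trial have persistent Grade 3" reactions or worse, or one or more has a serious adverse reaction, the dose is neither escalated nor expanded.

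In the event-free steps of 1.5.2, each move to a higher dose comes after a sentinel and three more participants have been reviewed. Step 3 reads "If the reactions are Grade 1-2, or transient Grade 3 that resolve within 24 hours, a sentinel participant may receive 5 µg" and step 5 reads "If the reactions are Grade 1-2, or transient Grade 3 that resolve within 24 hours, a sentinel participant may receive 10 µg". Step 7 opens the evaluation cohort "When all four participants to receive 10 µg have attended their follow-up visits at Day 7". Table 1 lists four participants at each of the three doses, which matches the Summary's count "in 12 individuals aged 18-45 years". The footnote to Figure 8 adds: "Reasons for a slower dose escalation include persistent Grade 3 or serious reactions".

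**The concern.** The stated minimum is lower after a severe reaction than without one, and lower at the higher doses than at the lower ones. The second escalation covers doses 2.5 to 10 times the previous maximum of 1 µg. Neither Section 1.5.2 nor the amendment list in Section 17 explains the change from four to one.

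The sentence can be read in two ways.

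- **Reading (a):** it replaces the reviews in steps 3 and 5. The next dose could then follow two people at the current dose, one of them with a persistent Grade 3 reaction.
- **Reading (b):** steps 3 and 5 still apply. The minimum of one then never binds, and the sentence misleads.

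At stake is how many people are observed at 2.5 or 5 µg, after one warning event, before anyone receives the next dose. The move on from 10 µg is not affected, because step 7 waits for all four participants.

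**Working it through.** **Which text governs after a sentinel event.** Steps 2 and 4 allow three further participants only if the sentinel's reactions were Grade 1-2 or transient Grade 3. A persistent Grade 3 reaction fails that condition. Steps 3 and 5 review the three people who would have been dosed under it. So the exception paragraph takes over, and the only number it gives for escalating is one.

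**Counts.**

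| Situation | Participants reviewed before the next dose |
|---|---|
| 1.5.1, after a sentinel event | 4 in total |
| 1.5.2, no event | 1 + 3 = 4 |
| 1.5.2, after a sentinel event, reading (a) | 2 (first sentinel with the event, second acceptable) |
| 1.5.2, after a sentinel event, reading (b) | at least 4 |

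**Timing, using the nominal 48-hour call.**

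- Event-free plan: sentinel at 0 h, three more at 48 h, next dose at 96 h.
- Reading (a): sentinel at 0 h, second sentinel at 48 h, next dose at 96 h.
- Four in total: sentinel at 0 h, second sentinel at 48 h, two more at 96 h, next dose at 144 h.

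Reading (a) is therefore no slower than a clean run.

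**Effect on the stop at two or more.** The protocol gives no persistent Grade 3 rate at 2.5 to 10 µg, so the true rate *p* is an assumption, with participants taken as independent. Given that the first sentinel has had the event, the stop fires before the next dose if at least one further participant also has it:

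- one further participant, reading (a): *p*
- three further participants, four in total: 1 − (1 − *p*)³

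The unconditional loss per dose level multiplies the difference by the chance of the sentinel event: *p* × [1 − (1 − *p*)³ − *p*].

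| Assumed *p* | Reading (a) | Four in total | Unconditional loss |
|---|---|---|---|
| 0.01 | 0.010 | 0.030 | 0.0002 |
| 0.05 | 0.050 | 0.143 | 0.0046 |
| 0.10 | 0.100 | 0.271 | 0.0171 |
| 0.20 | 0.200 | 0.488 | 0.0576 |

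For example, at *p* = 0.10: 1 − 0.9³ = 0.271, and 0.10 × (0.271 − 0.100) = 0.0171.

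Under reading (b) the loss is zero at every rate.

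**The case against.** The strongest reply is that a minimum is not a permission. Only steps 3 and 5 actually allow 5 or 10 µg to be given, and both come after three further participants have been reviewed. The Figure 8 footnote lists persistent Grade 3 reactions as a reason for going slower, which does not fit a next dose at 96 hours, and Table 1 plans four people per dose. This favours reading (b), and it stands as far as it goes. But the exception paragraph does not say that the steps continue. Section 1.5.1 has comparable steps and still states four in its own exception paragraph.

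Oversight is also real. Section 1.5.3 sends every persistent Grade 3 reaction to the Trial Steering Committee at once, Section 9.4 does the same for reactions that interrupt the enrolment plan, and Section 1.5 has experienced clinicians supervising. That reduces the exposure. It does not hold escalation after a single event: the pause for all participants in Sections 1.5.3 and 5.1.5 needs two persistent Grade 3 reactions in 20, or one serious adverse reaction.

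The two sentences also differ in kind: 1.5.2 wants acceptable data, whereas 1.5.1 wants only that data be provided. That makes 1.5.2 stricter about the one participant. It does not replace the other observations, and under 1.5.1 a second persistent Grade 3 reaction among the four would stop escalation anyway.

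Finally, the size is small and depends on assumed rates. Section 1.5.2 reports only absent, mild and infrequent moderate reactions at 1 µg or below. That neither supports nor rules out the higher rates in the table.

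**Conclusion.** The concern holds. Sections 1.5.1 and 1.5.2 share the trigger, the second-sentinel step and the stop, but state minimums of four and one, with no reason for the difference. Under reading (a), an early second signal is more likely to be missed before the next dose: at assumed rates of 1% to 20%, the chance of stopping in time after a sentinel event falls from 3–49% to 1–20%. Unconditionally this is about 0.02% to 5.8% per dose level, for the two levels concerned (2.5 and 5 µg). Under reading (b), which the footnote favours, no protection is lost, but staff must work out just after a severe reaction whether one participant or four are needed. The figures rest on assumed rates and independence between participants. The discrepancy in the text rests on neither. It should be corrected, because the rule matters most in the situation where it is unclear.

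**What to change.** In Section 1.5.2, replace the one-participant sentence with the standard of Section 1.5.1. Suggested content: escalation waits until at least four people at that dose, counting the affected sentinel, have safety data to at least 48 (±5) hours, and no second persistent Grade 3 reaction has occurred among them. The stop at two or more and the numbered steps stay as they are.

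The cost is one sentence. The affected sentinel, the second sentinel and two more make up the four per dose level already in Table 1, so nobody is added to the plan. If the sponsor takes steps 2 and 4 to mean three more after the second sentinel, that gives five, and a minimum worded as at least four does not lower it. Against reading (a), the next dose moves from about 96 to about 144 hours, roughly two days, and only after a sentinel event.

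Section 6.8 implies that the second cohorts may already be under way. If the escalation is complete, the sponsor should state which rule was applied and correct the text to match.

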### 1.5.3 EXPANDED SAFETY EVALUATION

Provided there are nothing worse than transient Grade 3 reactions in the safety data collected to Day 7 (minimum) from the first 42 participants to receive one vaccination at 1 µg, further centres will be able to start injections, accumulating data in at least 200 individuals for the expanded safety evaluation of the 1 µg dose at Week 0. This will inform the safety of lower doses and is the most efficient way to proceed prior to review of immune responses.

The restriction on upper age of 45 years will be removed from the database and participants up to age 75 years will be eligible for enrolment in the expanded safety evaluation in order to evaluate immune responses across a broader age range.

At any point during the trial, persistent Grade 3 reactions or any serious adverse reactions will be immediately reported to the Trial Steering Committee (TSC). If there are two participants with persistent Grade 3 reactions, or one with a serious adverse reaction, in the first 20, vaccinations will be paused in all participants and the TSC will be asked to review the accumulated safety data and make a recommendation. If vaccinations are paused in all participants, a substantial amendment will be submitted to the competent authorities. Likewise, approval from the competent authorities is needed before the study can be resumed.

Although the original intention was for participants in the expanded safety evaluation to receive a 1 µg dose at both the first and second vaccinations, the TSC recommended that a higher, and we hope more immunogenic, dose be given at the second vaccination. We will proceed with 10 µg, provided this is sufficiently well tolerated in the second dose escalation/evaluation. The TSC agreed that we should assess the Day 7 (minimum) safety data from 20 (minimum) participants at each dose level in the second dose escalation/evaluation cohort, before asking the TSC to recommend which dose to use for the second vaccination of participants in the expanded safety evaluation. We believe this decision will be made in time for vaccinations at Week 14 of the participants' schedule. Alternatively, participants can elect to receive the 1 µg dose at Week 4, as originally planned.

### 1.5.4 RATIONALE FOR CHOICE OF TRIAL POPULATION

First-in-human dosing for vaccine candidates is typically in healthy young adult populations as these individuals generate the most robust responses. However, it will be important to demonstrate immunogenicity in those most at risk of severe disease. As this risk increases with age, the upper age limit for the expanded safety evaluation is 75 years, recognising that government guidance on strict social distancing of the over 70 may make it difficult for participants over 70 years old to attend trial sites. All participants will provide samples for immunogenicity assessment, including measurement of titres of serum binding and neutralising antibodies, induction of high levels of which is believed to be essential for an effective vaccine. Thus we will be able to confirm immunogenicity of the vaccine in older participants.

Both male and female participants will be included and trial sites will attempt to keep an equal proportion, although the priority will be to ensure timely accrual to the trial.

In order to study the safety and immunogenicity of LNP-nCoVsaRNA vaccine in individuals with a history of SARS-CoV-2 infection, one investigator site (at St Mary's Hospital, London) will preferentially enrol participants known to have infection-induced SARS-CoV-2 antibodies prior to enrolment. The site's enrolment target is 30 participants.

## 2 SELECTION OF SITES/CLINICIANS

Sites and investigators were selected based on the project proposal and grant application.

### 2.1 SITE/INVESTIGATOR INCLUSION CRITERIA

To participate in the COVAC1 trial, investigators and clinical trial sites must fulfil a set of basic criteria that have been agreed by the COVAC1 Trial Management Group (TMG) and are defined below.

Each site will be issued with the appropriate COVAC1 master file documentation with the regulatory and ethics approvals and MRC CTU at UCL accreditation documents. Sites must complete the COVAC1 Accreditation Form for the trial at the same time as applying for their local approval.

#### 2.1.1 PI'S QUALIFICATIONS & AGREEMENTS

1. The investigators should be qualified by education, training, and experience to assume responsibility for the proper conduct of the trial at their site and should provide evidence of such qualifications through an up-to-date curriculum vitae and/or other relevant documentation requested by the Sponsor, the REC, the IRB, and/or the regulatory authorities.
2. The investigator should be thoroughly familiar with the appropriate use of the investigational products, as described in the protocol, in the current Investigator Brochure, in the product information and in other information sources provided by the Sponsor.
3. The investigator should be aware of, and should comply with, the principles of GCP and the applicable regulatory requirements. A record of GCP training should be accessible for all investigators.
4. The investigator/site should permit monitoring and auditing by the Sponsor, and inspection by the appropriate regulatory authorities.
5. The investigator should maintain a delegation log of appropriately-qualified persons to whom the investigator has delegated significant trial-related duties.
6. The investigator should sign an investigator statement, which verifies that the site is willing and able to comply with the requirements of the trial.

#### 2.1.2 ADEQUATE RESOURCES

1. The investigator should be able to demonstrate a potential for recruiting the required number of suitable subjects within the agreed recruitment period (that is, the investigator regularly treats the target population).
2. The investigator should have sufficient time to properly conduct and complete the trial within the agreed trial period.
3. The investigator should have available an adequate number of qualified staff and adequate facilities for the foreseen duration of the trial to conduct the trial properly and safely.

4. The investigator should ensure that all persons assisting with the trial are adequately informed about the protocol, the investigational product(s), and their trial-related duties and functions.
5. The site should have sufficient data management resources to allow prompt data entry and response to data queries from MRC CTU via a web-based eDC system.

### **2.1.3 SITE ASSESSMENT**

Each selected clinical trial site must complete the COVAC1 Accreditation Form for the trial, which includes the Investigator Statement, Signature and Delegation of Responsibilities Log, and staff contact details. The Investigator Statement verifies that the site is willing, and able to comply with the requirements of the trial. This will be signed by the Principal Investigator (PI) at the site. In addition and in compliance with the principles of GCP, all site staff participating in the trial must complete the Signature and Delegation of Responsibilities Log and forward this to the MRC CTU at UCL. The MRC CTU at UCL must be notified of any changes to trial personnel and/or their responsibilities. An up-to-date copy of this log must be stored in the Investigator Site File (ISF) at the site and also at the MRC CTU at UCL in the Trial Master File (TMF).

## **2.2 APPROVAL AND ACTIVATION**

The Clinical Trial Authorisation (CTA) for the trial requires that the Medicines and Healthcare products Regulatory Agency (MHRA) be supplied with the names and addresses of all participating site principal investigators, hence it is vital to receive full contact details for all investigators prior to their entering participants.

On receipt of the above documents at the MRC CTU at UCL, written confirmation will be sent to the PI and copied to Imperial College London. The site's pharmacist, or other person delegated by the PI, will also be informed of the site's activation and the vaccines will be dispatched to the named pharmacist, or other person delegated by the PI, in the Accreditation Form documents.

1. The site should conduct the trial in compliance with the protocol as agreed by the Sponsor and the regulatory authority, and which was given favourable opinion by the REC.
2. The PI or delegate should document and explain any deviation from the approved protocol, and communicate this with the trial team at the MRC CTU at UCL.

A list of activated sites can be obtained from the Trial Managers.

## **2.3 SITE/INVESTIGATOR EXCLUSION CRITERIA**

Sites which are unable to store the study vaccine at below  $-60^{\circ}\text{C}$  will be excluded.

